**Figure 3 figure3:**
[figure not shown]
Hemiablation.

### Patient Follow-Up

#### Postimplant Dosimetry

Post-plan quality assurance using magnetic resonance computed tomography (CT) fusion (MR-CT fusion) is required because it reduces inter-observer variation by improving prostate edge detection, and allows appreciation of treatment margins [61,62]. Fusion can be accurately performed to sub-millimeter accuracy using the seeds as fiducial markers. It is essential to use the appropriate MR sequences in order to facilitate both prostate contouring and seed localization. A Fast Spin Echo T2-weighted MR sequence is used, with the technical parameters described in Textbox 4.

Technical parameters used with the Fast Spin Echo T2-weighted MR sequence.ParametersRepetition time (TR) = 4500 msecEcho time (TE) = 90 msecEcho train length (ETL) =10,Pixel bandwidth (BW) = 580 Hz/pixelField of view = 20 x 20 cm3 mm slice thickness, 0 mm gapAcquired matrix size = 320 x 224 with phase encoding direction along rowsFlip angle = 90°

CT images are likewise obtained in the supine position, imaging the prostate and all seeds visible on the scout image in 2 mm slices. Aerated gel with Ultravist contrast is inserted for the pelvic CT for urethral localization by the oncologist. No specific bowel preparation is used before either scan but they should be performed sequentially, with the CT following the MRI generally within half an hour. Patients will also undergo a pelvic and chest x-ray to assess for any seed migration.

In order to improve this pilot trial consistency and check the hemi-implant quality, MR-CT fusion for all the participants will be reviewed by one of the two primary investigators with experience in MRI contouring and MRI-CT fusion; Dr [name] has performed more than 100 MRI-CT fusions.

#### Follow-Up Schedule

Routine assessment following completion of treatment includes PSA and clinical evaluation 4 to 6 weeks after the implant to manage and document any acute toxicity. The assessment will continue every 3 to 6 months depending on symptoms up to 3 years, and then every 6 to 12 months, with a PSA and digital rectal exam at each visit beyond 6 months up to 10 years. The IPSS, the International Index of Erectile Function (IIEF), and the Expanded Prostate Cancer Index Composite (EPIC) questionnaire are recorded at baseline and at each visit as is standard for all men receiving any type of prostate BT in the STGCCC. Specific follow-up for the study will involve a repeat Mp-MRI by 20 and 36 months and a TTGMB at 36 months. Patients will be followed up to 10 years after the implant, although the study finishes after 36 months of enrollment. Once we reach a median of 3-year follow-up (ie, sufficient time to determine rate of local control with the biopsies in 50% patients), then it would be adequate to commence the randomized controlled trial (RCT).

### Exit Strategy and Rescue Therapy

Biochemical failure will follow a PSA velocity greater than 0.75 ng/ml years in addition to nadir +2. Both parameters appear to better predict clinical failure after therapies that target less than the WG. Failure may also be proven on the TTGM control biopsies at 36 months or earlier in case of biochemical failure defined by Nguyen et al [51].

Definition of treatment failure will involve relapse in PTV or outside our PTV confirmed by biopsy. Relapse outside the PTV is not essentially a local treatment failure, and may be due to suboptimal patient selection. Due to the additional resources required to continue on this trial, these cases will be recorded as a treatment failure for further validation of the hemifocal BT as a treatment alternative to WG therapy. Interval from treatment to failure will be recorded.

After biochemical or local failure, the patient will exit the study. After appropriate investigations different salvage therapies can be offered to the patients who have failed. For local failure radical prostatectomy, HDR salvage BT or salvage cryotherapy in case of ipsilateral or contralateral relapse, or hemigland focal seed BT in case of contralateral relapse alone will be initiated. A choice of the treatment will be made after appropriate discussion in a multidisciplinary meeting and will be individualized.

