#### Secondary

Secondary study endpoints are (1) assessment of rectal, urinary, and sexual toxicity following hemiablative prostate seed BT; (2) change from baseline in quality of life indicators at specific time intervals using validated international questionnaires (IPSS, IIEF, EPIC) following hemiablative iodine-125 BT treatment; (3) evaluation of local tumor control in terms of biopsy outcomes after focal BT 36 months after completion of therapy; and (4) comparison of target coverage and relative doses to the rectum and the urethra for the same patient performing an hemigland treatment planning versus WG treatment planning and toxicity and quality of life after hemigland implant comparison with historical whole gland cohorts.

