##### Local Tumor Control

Local tumor control will include negative or indeterminate TTGMB 36 months after the treatment within the whole prostate. Definition of treatment failure will involve relapse in PTV or outside our PTV and confirmed by biopsy. In addition, dosimetric parameters and toxicity rates will be compared with historical WG treatment cohorts.

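### Men leave the study on a PSA trigger alone while local control is scored on the 36-month biopsy, so some exits cannot be classified and the secondary endpoints may lose the failures

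*Protocol article*

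**What the plan says.** Four rules in the protocol article bear on this point.

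- **Exit.** Under Exit Strategy and Rescue Therapy: "After biochemical or local failure, the patient will exit the study". Biochemical failure is defined there by PSA velocity together with the nadir-plus-2 rule, so a PSA result alone can trigger exit.
- **Failure.** The same section says: "Definition of treatment failure will involve relapse in PTV or outside our PTV confirmed by biopsy". It sets no time limit, and it allows an early biopsy: "Failure may also be proven on the TTGM control biopsies at 36 months or earlier in case of biochemical failure". Of relapses outside the planning target volume (PTV) it says "these cases will be recorded as a treatment failure for further validation of the hemifocal BT", and the time from treatment to failure is to be recorded.
- **Control.** Under Local Tumor Control: "Local tumor control will include negative or indeterminate TTGMB 36 months after the treatment within the whole prostate". The list of secondary endpoints fixes the time point: "evaluation of local tumor control in terms of biopsy outcomes after focal BT 36 months after completion of therapy".
- **Follow-up.** Follow-Up Schedule says "Patients will be followed up to 10 years after the implant", although the study itself finishes at 36 months. The abstract and the enrolment section also give 10 years. None of the three makes an exception for men who exit. Toxicity Evaluation Assessment requires toxicities above grade 1 to be followed until they resolve.

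**The concern.** The event that ends participation is wider than the event that counts as failure, and local control is scored at a visit that men who exit early do not reach as study participants. Three things follow.

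1. A man with a PSA trigger and a negative, indeterminate or absent early biopsy must exit. He does not meet the failure definition and has no 36-month study biopsy, so he has no outcome.
2. The denominator of the local control rate is open. If it were taken as the men biopsied at 36 months, early proven relapses would vanish from it. Indeterminate biopsies are scored as success, the most favourable choice, with no mention of reporting them apart.
3. If exit stops data collection, late toxicity and quality of life come from men who have not failed, and that subset would be set against historical whole-gland cohorts. No later analysis plan can recover data that were not collected.

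The article's hypothesis is similar disease control with less toxicity, and Follow-Up Schedule ties the timing of a randomised trial to having had time to determine the local control rate. These secondary results will therefore be read with weight.

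**Working it through.** The article states no expected control rate, failure rate or denominator, so there is no figure of its own to reproduce. The check has a textual part and an illustration.

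**Classification under the rules as written**

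| Course before 36 months | Exits? | Treatment failure? | 36-month control status |
|---|---|---|---|
| No trigger, biopsied at 36 months | No, unless that biopsy is positive | If positive | Defined |
| Early relapse, biopsy positive | Yes | Yes | Not stated how he enters the rate |
| PSA trigger, no positive biopsy | Yes | No | None |

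The third row is the gap that needs no assumption.

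**Illustration of size**

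Inputs: N = 20 implanted (Statistical Considerations). Assumed, because the article gives no counts: e early exits, all biopsy-proven relapses; b = 2 positive and i indeterminate biopsies at 36 months; all other men negative.

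- A, men biopsied at 36 months, indeterminate as control: (N − e − b)/(N − e)
- B, all implanted men, early failures not controlled, indeterminate as control: (N − e − b)/N
- C, all implanted men, negative biopsy only: (N − e − b − i)/N

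With e = 3 and i = 2 (exact Clopper-Pearson 95% intervals):

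- A = 15/17 = 88.2% (63.6 to 98.5)
- B = 15/20 = 75.0% (50.9 to 91.3)
- C = 13/20 = 65.0% (40.8 to 84.6)

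Range over e:

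| e | A | B | A − B (points) |
|---|---|---|---|
| 0 | 18/20 = 90.0% | 90.0% | 0 |
| 1 | 17/19 = 89.5% | 85.0% | 4.5 |
| 2 | 16/18 = 88.9% | 80.0% | 8.9 |
| 3 | 15/17 = 88.2% | 75.0% | 13.2 |
| 4 | 14/16 = 87.5% | 70.0% | 17.5 |

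Each indeterminate biopsy scored as control adds 1/20 = 5 points to B over C. With no early exits and no indeterminate biopsies, all three rates agree.

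**Exits on PSA alone**

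These do not all push the rate the same way. Take the 17 men biopsied at 36 months above (15 controlled) and one further man who exited on PSA with a negative biopsy. Leaving him out gives 15/17 = 88.2%; counting him as controlled gives 16/18 = 88.9%. Dropping him lowers the rate slightly.

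If k of the 3 early exits had no positive biopsy, the bounds over all implanted men run from 13/20 (every uncertain man not controlled) to (13 + 2 + k)/20:

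- k = 0: 65% to 15/20 = 75%
- k = 1: 65% to 16/20 = 80%
- k = 3: 65% to 18/20 = 90%

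**The case against.** The strongest reply is that no bias is written into the plan. Local Tumor Control says what counts as control; it does not say that early failures leave the denominator. The next sentence of that section repeats the failure definition without a time limit, and the exit section records the interval to failure. A natural reading is that an early proven relapse counts against local control. This stands. A reader might infer that the plan yields an inflated rate such as 15/17, or that every departure raises it. The first is permitted but not stated, and the second is false for a man who exits on PSA with a negative biopsy. The plan also makes two conservative choices: it counts relapse outside the PTV as failure, and it judges the whole prostate.

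A second reply is that exit may mean only leaving the study-specific tests. The article ties remaining on the trial to extra resources, describes follow-up apart from the 20- and 36-month assessments as standard, and says the questionnaires are routine at the coordinating centre. Separating data after salvage is defensible too, since salvage confounds toxicity. This is a possible reading, but the article does not state it. Its unqualified exit sentence stands beside an unqualified 10-year commitment, and routine collection is described for one centre of five.

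A third reply is that no local control threshold governs the randomised trial. That is correct: Follow-Up Schedule sets a timing condition, and the only numerical acceptability limit is more than 20% poor-quality implants. Finally, denominators are often left to an analysis plan that is not shown. That covers the rate, but not the mismatch between the exit and failure rules or the data that exit may cut off.

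**Conclusion.** The point holds as a defect in the secondary endpoints. Three parts rest on the text alone: exit on PSA without a positive biopsy leaves a man unclassified; indeterminate biopsies count as control; and the exit rule is not reconciled with follow-up to 10 years or with following toxicity until it resolves.

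The overstatement of local control is conditional. It arises only if early biopsy-proven failures are dropped from the denominator. For 0 to 4 such men among 20, with two positive 36-month biopsies, it is 0 to 17.5 points, plus 5 points per indeterminate biopsy relative to a negative-only rate. All these counts are assumptions. The loss of toxicity and quality-of-life data after exit is likewise possible rather than stated.

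The primary endpoint, dosimetric feasibility at day 30, is unaffected. This should be fixed, but it is not a condition for the trial to be sound.

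**What to change.** - **Denominator.** Report 36-month local control over all implanted men, with any biopsy-proven relapse up to 36 months counted as not controlled.
- **Uncertain outcomes.** Report biochemical failure without a positive biopsy, indeterminate biopsies and missing biopsies as separate categories. Give best- and worst-case bounds next to the pre-specified rate that counts negative or indeterminate as control.
- **Exit.** Reconcile the exit rule with the abstract, the enrolment section, Follow-Up Schedule and Toxicity Evaluation Assessment. State that, for data collection, exit ends only the study-specific tests, and that toxicity, questionnaire and PSA data from routine visits are still collected at all centres, flagged from salvage onward.

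The cost is protocol wording and slightly more data handling. The questionnaires are already routine at the coordinating centre; the other centres would need to confirm the same. The reported control rate may look less favourable, and the bounds will be wide with 20 men.

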### Study Endpoints

#### Primary

Feasibility of the hemigland focal therapy (the delivery of the prescription dose to half of the prostate) using a BT seed implant, while respecting standard tolerance doses of adjacent normal organs is the primary study endpoint.

#### Secondary

Secondary study endpoints are (1) assessment of rectal, urinary, and sexual toxicity following hemiablative prostate seed BT; (2) change from baseline in quality of life indicators at specific time intervals using validated international questionnaires (IPSS, IIEF, EPIC) following hemiablative iodine-125 BT treatment; (3) evaluation of local tumor control in terms of biopsy outcomes after focal BT 36 months after completion of therapy; and (4) comparison of target coverage and relative doses to the rectum and the urethra for the same patient performing an hemigland treatment planning versus WG treatment planning and toxicity and quality of life after hemigland implant comparison with historical whole gland cohorts.

#### Measurement of Endpoints

##### Feasibility

Dose parameters for prostate (V100, V150, V200), rectum (V100), and urethra (D5, D30) will be recorded for the hemigland and the WG treatment planning. Dosimetric parameters in the post-implant dosimetry at day 30 for WG BT are well defined in the literature and they are correlated to efficacy and toxicity. The post-implant dosimetric study for hemigland BT patients will aim for the same dosimetric parameters at day 30 after the implant for tumor coverage and organs at risk dose.

##### Toxicity Evaluation Assessment

Patients will be assessed on the day of enrollment, at 4 to 6 weeks, and every time they come back for follow-up (every 6 months) to determine acute, sub-acute, and late toxicity after the implant in the urinary, rectal, and sexual domain. An adverse event is any deleterious effect which may occur as a result of the intervention. Treatment-related toxicities will be graded using the National Cancer Institute Common Terminology Criteria for Adverse Events (CTCAE) Version 4.0 as follows: (1) grade 0 is no adverse events, (2) grade 1 is mild events not requiring intervention, (3) grade 2 is moderate events interfering with normal activities, (4) grade 3 is severe events causing inability to carry out normal activities, (5) grade 4 is life threatening or disabling events, and (6) grade 5 is death (Figure 4). A follow-up assessment will be undertaken within seven days in patients reporting greater than grade 1 toxicities, and will continue in this manner until toxicity has resolved, with documentation of action taken at each time point. Failure of an adverse event to resolve and its translation to chronicity at a given time point will be documented by the clinician. Serious adverse events (grade 3 or greater) will require assessment by the clinician and documentation of action taken.

**Figure 4 figure4:**
[figure not shown]
The necessary data to be collected at various time points of the study.

##### Quality of Life

Quality of life will be assessed using the IPSS, IIEF, and EPIC questionnaires. The change from baseline will be measured at specific time points (Multimedia Appendix 1).

##### Local Tumor Control

Local tumor control will include negative or indeterminate TTGMB 36 months after the treatment within the whole prostate. Definition of treatment failure will involve relapse in PTV or outside our PTV and confirmed by biopsy. In addition, dosimetric parameters and toxicity rates will be compared with historical WG treatment cohorts.

### Data Collection

The necessary data to be collected at various time points of the study is outlined in Figure 4.

### Statistical Considerations

It is anticipated that a sample size of 20 patients will be accrued to enable the investigator to deliver hemiablative seed BT with a reasonable amount of confidence. This feasibility study will proceed in 5 participating centers. Failure to accrue 15 patients in 24 months will initiate early closure of this study. The time-frame for completion of recruitment will be approximately 12 months, with a further 24 months required for collection of acute and late toxicity data, maturation of quality of life data, and correlation with the biopsy by 36 months.

We do not consider it necessary to use early stopping rules for poor quality implants (not adequate dosimetric parameters on day 30), or acute treatment-related toxicities because of the low number of patients we are aiming for. An analysis will be performed after 20 patients have participated in the study. Therefore, if greater than 20% of patients have poor quality implants, this procedure will be unacceptable.

Descriptive statistics will be used to describe the frequency at which prostatic cancer low grade disease can be seen on Mp-MRI, and the frequency of unilateral prostatic disease is found after a mapping of the prostate. In addition to standard PSA follow-up, response will be assessed by imaging at 20 and 36 months as well as by TRUS-guided biopsy at 36 months.

Data analysis will be undertaken by [name] with the assistance of a qualified statistician.

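### The 12 + 24 month timetable ends at about the time the first 36-month biopsy falls due; all 20 biopsies need about 48 months

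*Protocol article*

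**What the plan says.** Statistical Considerations gives the size and the timetable: "It is anticipated that a sample size of 20 patients will be accrued"; "completion of recruitment will be approximately 12 months, with a further 24 months required for collection of acute and late toxicity data". That sentence goes on to include maturing quality-of-life data and correlation with the biopsy by 36 months. The accrual safeguard in the same section reads: "Failure to accrue 15 patients in 24 months will initiate early closure of this study".

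Local control is a secondary endpoint. The Local Tumor Control section counts as controlled a "negative or indeterminate TTGMB 36 months after the treatment within the whole prostate". The sections Investigations, Secondary (under Study Endpoints) and Budget and Funding likewise time the biopsy 36 months from treatment. Investigations and Budget and Funding put the last multiparametric MRI at the same point.

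Follow-Up Schedule says that "the study finishes after 36 months of enrollment", with patients followed for as long as 10 years. It considers a median follow-up of 3 years adequate for commencing a randomised trial, describing this as "sufficient time to determine rate of local control with the biopsies in 50% patients".

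**The concern.** Two clocks have been treated as one. The 12 + 24 month total runs from the opening of recruitment, whereas the biopsy clock starts at each man's implant. The sum equals 36, which is also the biopsy month, and this makes the timetable look sufficient. For the last man recruited, the stated window leaves about 24 months of follow-up, a year short of his biopsy.

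The duration sentence itself claims to cover the biopsy, so this is a figure that is wrong as written, not a detail left to a fuller document. If analysis, staffing or funding were planned to that figure, the scheduled 36-month biopsies and MRIs would fall almost entirely after it. Budget and Funding charges these tests to an internal hospital research budget, so the stated duration has practical weight.

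**Working it through.** **Inputs.** 20 patients, about 12 months of recruitment, 24 further months, and a closure rule of 15 patients in 24 months (all from Statistical Considerations). Biopsy at 36 months after treatment (Local Tumor Control and the other sections above). Assumptions of mine: uniform accrual, and a lag from enrolment to treatment of 0 to 3 months, since the article gives neither.

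**The plan's own figure.** 12 + 24 = 36 months from the start of recruitment. This reproduces, and it matches the 36 months in Follow-Up Schedule if that is counted from study start.

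**Biopsies due at month 36.** A man treated in month *m* is due at month *m* + 36. A biopsy is due by month 36 only if *m* = 0. This holds whatever the accrual pattern: 0 of 20 are due, or 1 of 20 if the first man is treated on the day recruitment opens.

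**Follow-up at month 36.** It equals 36 − *m*. For *m* between 0 and 12 it runs from 36 − 12 = 24 to 36 − 0 = 36 months. With uniform accrual the median is 36 − 6 = 30. With a 3-month lag the range is 21 to 33.

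**When the biopsies fall due.**

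| Scenario | Median follow-up reaches 36 months | Last biopsy due |
|---|---|---|
| 20 men over 12 months, no lag | 6 + 36 = month 42 | 12 + 36 = month 48 |
| Same, 3-month lag | month 45 | month 51 |
| 20 men over 24 months, no lag | 12 + 36 = month 48 | 24 + 36 = month 60 |
| 15 men by month 24, same rate continued, no lag | 16 + 36 = month 52 | 32 + 36 = month 68 |

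The last row uses 15/24 = 0.625 men per month, so that 20 men need 20/0.625 = 32 months, with the midpoint at 16. That pace satisfies the closure rule.

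**Precision of half against all of the biopsies** (exact 95% Clopper–Pearson intervals, illustrative outcomes):

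| Controlled | Interval |
|---|---|
| 9/10 | 55% to 99.7% |
| 18/20 | 68% to 98.8% |
| 10/10 | 69% to 100% |
| 20/20 | 83% to 100% |

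**The case against.** The best reply is that nothing in the protocol cancels a biopsy falling after month 36. The biopsy is scheduled per patient and budgeted, and follow-up runs to 10 years. A reader might infer that local control cannot be read out at all; the documents do not support that. What fails is the stated duration.

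The end-of-study phrase in Follow-Up Schedule can also be read per patient, as the point where study-specific tests stop and routine follow-up continues. On that reading it nearly fits the biopsy, apart from any lag between enrolment and implant. The 24 months in Statistical Considerations still do not fit: counted from the close of recruitment they leave the last man a year short, and counted per man they leave every man a year short.

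A reader might also conclude that starting a randomised trial on half of the biopsies is an error. It is not one. The article discloses that choice for a pilot and does not present it as the final local-control analysis. The Discussion places the move to a randomised trial after feasibility, toxicity, quality of life and local control have been evaluated, so the decision does not rest on about 10 biopsies alone. The trigger falls after month 36, which shows that later data are expected, but that is a further reason to correct the duration.

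Nor does the closure rule support a 60-month ceiling. It sets a minimum of 15 men by month 24 and no limit on the time to reach 20.

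It also stands that earlier information will exist. Exit Strategy and Rescue Therapy allows an earlier biopsy on biochemical failure, and with 12-month accrual and no lag every 20-month MRI is due by 12 + 20 = month 32.

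**Conclusion.** The point holds as an inconsistency between the stated duration and the timing of a secondary endpoint. On the stated timetable essentially 0 of 20 scheduled biopsies are due at the end. The window is about 12 months too short with 12-month accrual, and more if accrual is slower or treatment lags enrolment. No passage reconciles the figures.

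The near-zero count and the 12-month shortfall follow from the protocol's own numbers. The median of 30 months and the month-42 trigger rest on uniform accrual with no lag.

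Severity is moderate. The primary endpoint, dosimetric feasibility assessed at day 30, is untouched, as is the rule on the proportion of poor implants. Eligibility, treatment and sample size do not change.

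**What to change.** In Statistical Considerations, replace the 24 further months with 36 months after the last implant, plus time for biopsy read-out. State the total as about 48 months with 12-month accrual and longer if accrual is slower, without a fixed upper bound.

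In Follow-Up Schedule, state that the study-specific period ends at the last treated patient's 36-month biopsy, and that routine follow-up continues to 10 years. Add that the final local-control rate is reported on all treated patients with an exact confidence interval. If results are looked at when about half of the biopsies are in, label that look as interim.

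The cost is a few sentences and a stated duration about 12 months longer, or more with slow accrual. No extra patients or procedures are needed, because every test concerned is already scheduled. The sponsor should check that the research budget covers the corrected period.

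### The plan rejects any stopping rule for poor implants, yet its own 20% criterion is mathematically settled at the fifth poor implant, after which nothing halts enrolment

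*Protocol article*

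**What the plan says.** All the relevant text is in the protocol article, Statistical Considerations.

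- Size: "It is anticipated that a sample size of 20 patients will be accrued".
- Stopping for quality: "We do not consider it necessary to use early stopping rules for poor quality implants", where poor quality is glossed as "not adequate dosimetric parameters on day 30". The same sentence also declines a rule for acute toxicity. The reason given is "because of the low number of patients we are aiming for".
- Timing: "An analysis will be performed after 20 patients have participated in the study".
- Criterion: "if greater than 20% of patients have poor quality implants, this procedure will be unacceptable".
- The one early closure described concerns recruitment: "Failure to accrue 15 patients in 24 months will initiate early closure of this study".

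Elsewhere, Postimplant Dosimetry has a primary investigator review the MR-CT fusion of every participant, but attaches no consequence for enrolment to what is found. No other section pauses or closes enrolment because of implant quality.

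**The concern.** A small sample is a fair reason to avoid interim hypothesis tests, which cost power or error. It is not a reason to ignore a result that is already fixed. The criterion is a count out of a planned 20, so there is a point after which no later implant can alter it. Beyond that point each further implant adds nothing to the pass/fail answer on the primary endpoint.

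At stake is how many men could receive a permanent implant with a technique that can no longer meet the trial's feasibility criterion. The Introduction itself treats an adequate implant as the safety measure. The feasibility subsection under Measurement of Endpoints notes that day-30 parameters are related to efficacy and toxicity, although it says this of whole-gland treatment.

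**Working it through.** **Inputs from the protocol.** Planned n = 20, single arm. Criterion: more than 20% poor. Quality is known at day 30. Recruitment: "The time-frame for completion of recruitment will be approximately 12 months". The plan states no alpha, power or expected poor-implant rate, so n = 20 cannot be re-derived and there is no operating figure to reproduce.

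**Assumptions.** The true poor-implant rate p is assumed, from 5% to 50%. Implants are treated as independent with constant p.

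**Step 1: the threshold as a count.** 4/20 = 20.0% does not exceed 20%; 5/20 = 25% does. So the criterion is X ≥ 5. After five poor implants, the final share is at least 5/20 = 25% even if every remaining implant is adequate. If the study ended with 15 men, 3/15 = 20% would pass and 4/15 = 26.7% would fail, so five would still exceed the limit.

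**Step 2: curtailment does not change the verdict.** Let T be the patient number of the fifth poor implant. The event T ≤ 20 is the same event as X ≥ 5 among 20, so P(unacceptable) is identical with or without closing at T:

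P(X ≥ 5) = 1 − Σ(x = 0 to 4) C(20, x) p^x (1 − p)^(20 − x)

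P(T = t) = C(t − 1, 4) p^5 (1 − p)^(t − 5), for t = 5, …, 20

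**Step 3: the day-30 lag.** Twenty men in 12 months gives 20/365 × 30 = 1.64 men per 30 days, rounded up to 2. The number implanted after the fifth poor result is known is max(0, 20 − T − 2). The chance that this is at least one is P(T ≤ 17).

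**Step 4: results.**

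| True poor rate | P(X ≥ 5) | Mean T, if criterion met | P(at least one man implanted after fifth is known), lag 2 | Mean such men if criterion met, no lag | Same, lag 2 | Mean over all trials, lag 2 |
|---|---|---|---|---|---|---|
| 5% | 0.003 | 17.2 | 0.001 | 2.9 | 1.5 | 0.0 |
| 10% | 0.043 | 16.7 | 0.022 | 3.3 | 1.8 | 0.1 |
| 20% | 0.370 | 15.6 | 0.242 | 4.4 | 2.8 | 1.0 |
| 30% | 0.762 | 13.9 | 0.611 | 6.1 | 4.3 | 3.2 |
| 40% | 0.949 | 11.9 | 0.874 | 8.1 | 6.2 | 5.8 |
| 50% | 0.994 | 9.9 | 0.975 | 10.1 | 8.1 | 8.0 |

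**Step 5: sensitivity to the lag.** At p = 40%, lags of 0, 1, 2 and 3 patients give mean numbers of 8.1, 7.1, 6.2 and 5.2 when the criterion is met. At p = 30% they give 6.1, 5.1, 4.3 and 3.5. At the slowest accrual the plan tolerates (15 in 24 months), 15/730 × 30 = 0.62 men are implanted per 30 days, so the lag would be nearer one patient.

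**The case against.** The strongest reply is that this is a disclosed choice with a reason, not an error. The 20% criterion belongs to the single analysis after 20 patients. A reader might infer that the plan has already declared the procedure unacceptable at the fifth poor implant. The text does not support that: the verdict is settled arithmetically, but declared only at the analysis.

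A reader might also infer that the plan obliges the investigators to go on implanting. It does not. It says formal rules are unnecessary, and it forbids neither the investigators nor the ethics committee from halting. Because a primary investigator reviews every fusion, a run of failures would be noticed. What remains is that halting is left to discretion when the plan's own criterion already marks the point.

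The size can be overstated too. Quoting about 8 men at a 40% poor rate ignores the day-30 lag; about 6 is the fair figure. Nothing in the protocol supports 40% in particular. Under Interventions the teams must perform at least 40 cases a year and the lead centre reports more than 1000 procedures. That does not establish a low rate for hemigland implants, but it makes the lower rows of the table relevant, and there the exposure is negligible. The protocol gives no turnaround time for the fusion review, so the lag may exceed 2 patients.

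Poor quality is a dosimetric label, not an observed harm, and normal-tissue tolerance has priority in planning. Implants beyond the fifth failure would also sharpen the estimated poor-implant rate and inform the secondary endpoints. These points limit the severity. None of them shows that the small sample justifies having no halt once the result is fixed.

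**Conclusion.** The point holds as a cheap improvement of minor to moderate severity. The stated reason does not support the choice: acting on a fifth confirmed poor implant needs no interim test, costs no error or power, and cannot reverse the primary conclusion.

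The practical size depends wholly on the unstated poor-implant rate. With a 2-patient lag, exposure is negligible at 10% or below. At 20% there is roughly a one-in-four chance that at least one man is implanted after the result is settled and known, and exposure is substantial at 30% and above. These figures rest on independence, a constant rate, even accrual and prompt reading at day 30.

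The point does not extend to the acute-toxicity half of the same sentence. The plan sets no toxicity threshold there, so there is no equivalent point at which a verdict becomes fixed.

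**What to change.** Reconcile the two statements in Statistical Considerations by curtailing enrolment at the plan's own criterion. For example: no interim hypothesis test is planned; a central count of confirmed poor-quality day-30 implants is kept as results are reviewed; once that count exceeds 20% of the planned 20 (that is, reaches five), enrolment closes and the trial reports that the procedure failed its feasibility criterion; men already treated continue follow-up as planned. This adds no clinical criterion. Management of men registered but not yet implanted stays with the investigators.

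Costs:

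- **Running count.** Results from 5 centres must be pooled promptly, with a stated turnaround for the fusion review. The review itself is already planned for every participant.
- **Fewer men for secondary endpoints.** This arises only in a trial that has failed its primary criterion. The Discussion already makes evaluation of toxicity, quality of life and local control follow from feasibility.
- **Estimation.** After early closure the crude poor-implant rate is biased upward, so the estimate must allow for the curtailment. For illustration, ignoring the lag: if the fifth poor implant is patient 12, the crude rate is 5/12 = 0.42, whereas the unbiased estimator for sampling stopped at the fifth event is (5 − 1)/(12 − 1) = 4/11 = 0.36. Results still pending at closure should be reported as well.
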